### Study Sample Size and Duration

The only analogous trial published, to our knowledge, is an RCT by Fereidouni et al [28], which also used the BSS to measure changes in SI, but in a depressed inpatient population. They reported a required sample size of 31 per arm, which was increased to 35 to account for attrition, calculated using a CI of 95%, a statistical power of 80%, and a minimum clinically significant difference of 5%. This previous trial enrolled 70 participants and had no dropouts.

In this study, the overall target sample size is 80 participants (40 in each group). To detect a within-group change (pre- and posttreatment changes in rating scale measures) of Cohen *d*=0.50, applying a 2-tailed α level of .05 and power at 0.80 (0.75 for between-group changes), the study will require 32 participants in each group. Our target sample size of 40 participants per group was chosen to account for an anticipated attrition rate of 20%, resulting in samples no smaller than 32. The attrition rate is based on clinical experience, as well as the literature reporting a mean dropout rate of approximately 18% in previous EMDR trials [29,51].

### Clinical Safety Procedures

To ensure participant safety during the study, the following measures have been instituted:

All participants must have access to a health professional, such as a family physician or psychiatrist, during the course of this trial, who is willing to provide general mental health care, as necessary. If a safety concern arises during the study, the participant’s provider will be informed.Before commencing EMDR, the participant will confirm their address, phone number, email address, and emergency contact person. This is necessary so that an emergency response can be activated if clinically indicated.If the participant is enrolled in the EMDR treatment group, the study therapist will ensure that a written safety plan has been completed before treatment is initiated. This safety plan will include helping the participant to identify their warning signs for crisis, their internal coping resources, sources of helpful distraction, and helpful others, including professional resources, from whom they can access assistance in a crisis. Contact information for Edmonton crisis services will also be provided.To ensure safety during EMDR sessions, participants will be asked to ensure that there is a supportive person who will be available to assist within 5 minutes, in the unlikely case of an emergency.If there is a significant worsening in SI, the study therapist may pause EMDR and focus on crisis stabilization and the institution of the individualized safety plan.The study research assistant (RA) was trained in a protocol for enrolling participants, which includes a safety protocol to manage any unanticipated situations in which a participant spontaneously expresses worsening or active SI (Multimedia Appendix 1). Consent for EMDR therapy includes an understanding that in the case of imminent risk of harm to self or others, the therapist or RA may need to activate the safety plan or call emergency services.For the EMDR group, adverse events will be queried and recorded at the beginning of each EMDR session, along with recording a self-report of the intensity of various symptoms, including SI, on a 0-10 scale. As therapy is taking place in the context of clinical care, progress will be documented in the electronic health record, which may be accessed by the participants’ treatment team (see Multimedia Appendix 2 for the items captured regarding adverse events). In addition, serious adverse events will be directly reported to the participants’ treatment team. Each person participating in the study must agree to maintain a relationship with his or her community treatment team during the study to avoid a situation where the person has no access to care during or immediately after participating in the study.

Participant confidentiality and web-based security:

Informed consent for web-based EMDR therapy also includes an agreement that the patient will disclose their physical location, keep a working telephone with them in the case of internet disconnection, and connect in a private area. Health service–level encrypted Zoom, as authorized by Alberta Health Services, will be used for videoconferencing therapy to minimize security concerns. The participants will also be encouraged to use their own private computer and Wi-Fi.Encryption will be used in the case that email is needed to send potentially identifying information, in accordance with Alberta Health Services policy.

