**Objective:**

The primary aim of this randomized controlled trial is to investigate whether remotely delivered EMDR (targeting experiences associated with suicidal thinking) reduces suicidal thoughts. Secondary aims include examining the impact of remotely delivered EMDR on symptoms of depression, anxiety, posttraumatic stress, emotional dysregulation, and dissociation. We will also report on adverse events in the EMDR group to explore whether targeting suicidal ideation with EMDR is safe. Finally, we will compare dropout rates between the treatment groups.

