**Conclusions:**

The results of this trial will contribute to knowledge on whether web-based delivery of EMDR is a safe and effective treatment for reducing suicidal ideation and potentially reducing the incidence of suicide attempts in this patient population.

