A further objective is to report on the history of ACEs and the level of dissociative symptoms experienced by study participants (EMDR vs treatment as usual [TAU] group), as these may be markers of complexity [39,40]. Dissociative symptoms have been linked to increased comorbidity, exposure to childhood adversities, clinical severity, and lower response to trauma-focused therapies (TFTs) [39-42]. There is controversy as to whether dissociation is a barrier to using TFTs, such as EMDR [43]. The dissociative subtype of PTSD has been associated with midline prefrontal inhibition of limbic regions involved in emotion regulation, leading to emotional overmodulation [42]. One possible clinical implication is that such patients may have difficulty improving with TFTs because of impaired emotional regulation capacities and a tendency to dissociate upon exposure to distressing cues inherent in the processing of the trauma. This could impair the ability to adequately activate the fear network, leading to reduced effectiveness of TFTs [42]. Therefore, measuring dissociation at baseline and after treatment will provide important information about whether EMDR impacts dissociation, or if dissociative symptoms adversely impact treatment response.

We will compare dropout rates between treatment groups and report on any adverse events that arise in the EMDR group to explore the safety of using EMDR to target SI. Experts in the field of trauma have long believed that survivors of trauma should be treated using a phased approach [44-46]. The first phase focuses on stabilization and the introduction of coping skills to reduce self-harm and suicidality. Once phase 1 is completed and the person is no longer a risk to themselves or others, phase 2 may begin, with TFTs such as EMDR, which focus on distressing memories directly. However, this phased approach emphasizing stabilization before trauma processing has been criticized as lacking evidence [47]. Therefore, studies reporting on the safety of TFTs, such as EMDR, in patients with SI can help address this controversy.

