## Methods

### Study Design

The study is a nonblinded RCT that will evaluate the effects of remotely delivered EMDR in combination with TAU, compared with TAU alone for adult patients with SI. Owing to the nature of EMDR, trial blinding to the research team and clinical staff is not possible. All clinical contact will occur on the web via a health care–level encrypted Zoom platform. The anticipated flow of participant enrollment is shown in Figure 1, and details are included in the *Study Procedure* section. Participants will be randomized (by computer-generated random allocation) to receive either intensive 90-minute EMDR sessions twice per week plus TAU or TAU alone. A pilot study by Proudlock et al [29] and an RCT by Fereidouni et al [28] used a similar design, with intensive EMDR provided 2 to 3 times per week. In the study by Proudlock et al [29], most of the participants were outpatients with an acute mental health crisis with SI. In the RCT, the participants were inpatients with major depression and suicidal thoughts [28]. The literature suggests that intensive (ie, multiple sessions per week) therapy is safe and effective and may reduce attrition [28,29,48,49].

The primary outcome is the intensity of SI in adults, as measured by the BSS and the CSSRS. Secondary outcomes include mood (Beck Depression Inventory-II and Patient Health Questionnaire 9), anxiety (Generalized Anxiety Scale-7), posttraumatic symptoms (Impact of Events Scale Revised), dissociation symptoms (Dissociative Experiences Scale-II [DES-II]), and emotion dysregulation (Difficulties in Emotional Regulation Scale). Secondary outcomes include adverse events and dropout rates. A subsequent longer-term analysis, beyond the scope of this protocol, will examine differences between groups with respect to the number of emergency room visits, hospitalizations, and overall health care use in the year before and after therapy.

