EMDR will specifically target the traumatic memories or core beliefs associated with the SI. These targets may be easily identified by the patient in some cases. Alternatively, the standard floatback method may be used to identify memory targets, or therapists may target the somatic urge or state associated with suicidal thoughts. This strategy of targeting states or urges has been utilized in EMDR protocols such as the *DeprEnd protocol* for depression and the *DeTUR protocol* for urges associated with substance use disorders [58,59]. Other possible targets for EMDR include memory of the circumstances surrounding the first occurrence of SI, memories at the origin of the negative beliefs associated with SI, or memories related to hopelessness and despair [21,58,60]. If escape fantasies, including the fantasy of escaping through suicide, emerge during memory processing, the participant may be encouraged to notice the fantasy rather than avoid or suppress it. In addition, if nightmares arise during the course of treatment, they can also be targeted directly using EMDR if clearly related to SI or the experiences being reviewed in therapy sessions.

Participants will be seen twice weekly until the therapy is completed (12 desensitization sessions in total). Symptoms and any adverse reactions will be recorded at the beginning of each session using a standard EMDR session progress note form.

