##### Columbia Suicide Severity Rating Scale

The CSSRS is a questionnaire used for suicide assessment, developed by multiple institutions including Columbia University. Several versions exist; this study will use the clinician-rated version that assesses lifetime and recent SI (last week) and suicidal behavior at baseline. In addition, a self-report version will be used at baseline, 2 months, and 4 months to assess SI in the *past 1 week*, which includes 5 questions about SI and 2 questions about suicidal behavior [62].

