##### Session Forms

For the EMDR group, session forms will be used to track weekly progress. These forms include a scale of 0 to 10 (ranging from no difficulties to highest intensity) to record the intensity of suicidal thoughts, self-harm urges, and the following symptoms: worry thoughts, anxiety, guilt or shame, anger, sadness, flashbacks, sleep problems, substance use, suicidal thoughts or impulses, self-harm urges, concentration difficulties, lethargy or fatigue, appetite problems, and repetitive thoughts. These forms will also capture the session focus and any deviations from the standard EMDR protocol.

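### Adverse events are actively queried and reported only in the EMDR arm, so this secondary outcome has no randomised comparator

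*Protocol article*

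**What the plan says.** The Study Design section of the protocol article states: "Secondary outcomes include adverse events and dropout rates". No arm is specified there. The Abstract's Conclusions say the results will help show "whether web-based delivery of EMDR is a safe and effective treatment for reducing suicidal ideation".

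Wherever collection or reporting is described, it is confined to one arm:

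- Abstract, Objective: "We will also report on adverse events in the EMDR group to explore whether targeting suicidal ideation with EMDR is safe".
- Introduction, Objectives: "We will compare dropout rates between treatment groups and report on any adverse events that arise in the EMDR group to explore the safety" of the approach. Dropout is two-arm and adverse events one-arm within the same sentence.
- Clinical Safety Procedures: "For the EMDR group, adverse events will be queried and recorded at the beginning of each EMDR session".
- Session Forms, which include suicidal thoughts and self-harm urges: "For the EMDR group, session forms will be used to track weekly progress".
- Results: the adverse effects to be reported are those that emerge under EMDR treatment.

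The session queries follow the therapy schedule: "Participants will be seen twice weekly until the therapy is completed (12 desensitization sessions in total".

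Table 1, which governs what every participant completes through REDCap, has no adverse-event item. It does give both arms the BSS and the self-rated CSSRS at all three time points. For the CSSRS, "a self-report version will be used at baseline, 2 months, and 4 months to assess SI in the *past 1 week"; that version carries two questions on suicidal behaviour. BSS question 20 asks about previous attempts, and no one-week limit is stated for that item.

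**The concern.** The safety question is a causal one. The Ethics section records the fear that exposure to traumatic memories may worsen suicidality, and the Objectives section sets out the dispute over whether stabilisation must come first. The Discussion adds that a favourable result would challenge current practice.

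Every participant enters with suicidal ideation, so some attempts, self-harm, crises or admissions may occur in either arm regardless of EMDR. A count from the EMDR arm alone may look alarming when it equals background, or reassuring when it exceeds it. The randomised TAU group could tell these apart, but as described it is not asked.

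This is a matter of data collection. An analysis plan cannot recover TAU events that nobody asked about, so it is not a detail that an article may leave to the SAP.

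**Working it through.** **Plan's own figures.** The article gives no figure for safety. Its group sizes supply the denominators and they reproduce. For a within-group d of 0.50, two-sided alpha 0.05 and power 0.80, the normal approximation gives ((1.960 + 0.842)/0.50)² = 31.4, rounded up to 32; 32/(1 − 0.20) = 40.

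**1. Query points per arm.** Clinical Safety Procedures and Study Procedure give EMDR 12 session queries at two per week, so 12/2 = about 6 weeks. For TAU, none is described.

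**2. Coverage of the CSSRS windows (both arms).** Four months is 4 × 365.25/12/7 = 17.4 weeks. Two one-week windows cover 2/17.4 = 11.5% (2/16 = 12.5% if a month is taken as four weeks). About 88% of follow-up lies outside them.

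**3. What that coverage means for TAU.** Assume, for illustration, four suicidal-behaviour events in the arm, independent and spread evenly over follow-up.
- Expected number inside a window: 4 × 0.115 = 0.46 (0.50 on 16 weeks).
- Chance of capturing at least one: 1 − (1 − 0.115)⁴ = 39% (41% on 16 weeks).

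These figures concern the CSSRS alone. BSS question 20 adds attempt information in both arms, but as described it is undated and mixes attempts before and after baseline. It does not ask about other self-harm, crises or admissions.

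**4. What a one-arm count can show.** With zero events in n participants, the upper limit is 1 − 0.05^(1/n) one-sided and 1 − 0.025^(1/n) two-sided.

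| n in EMDR arm | one-sided 95% | two-sided 95% |
|---|---|---|
| 40 | 7.2% | 8.8% |
| 32 | 8.9% | 10.9% |

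No TAU rate is available to set against these limits.

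**5. What equal collection would give.** Power of a two-sided comparison at alpha 0.05, for assumed event rates:

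| rates | 32 per arm | 40 per arm |
|---|---|---|
| 5% vs 15% | 0.26 | 0.32 |
| 5% vs 20% | 0.44 | 0.53 |
| 10% vs 30% | 0.52 | 0.61 |

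Equal collection would remove the difference in ascertainment between arms, but the comparison would remain descriptive.

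**The case against.** The best defence is that this is an openly declared, exploratory, one-arm adverse-event report, and that much other safety information is comparative. Most of that is true, and it rules out several stronger readings that a reader might infer.

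- **That the safety question has no comparator at all.** Not supported. BSS and CSSRS severity, depression, anxiety, post-traumatic, dissociative and dysregulation scales are collected in both arms, and the Statistical Analysis section makes EMDR versus TAU the main contrast. Dropout is also compared. Only adverse events lack a comparator.
- **That suicidal behaviour in TAU is seen only in two one-week windows.** True of the CSSRS, but BSS question 20 is given to both arms and lies outside the items that may be skipped. It can point to an attempt between visits, though imperfectly.
- **That admissions and emergency visits in TAU will never be examined.** Study Design announces a between-group comparison of health care use, but places it beyond this protocol.
- **That EMDR will show about four times as many events at equal true rates.** This comes from (6 + 2)/2 weeks of coverage and requires pooling session reports with CSSRS answers. No such analysis is planned, and the figure assumes no overlap between sessions and windows.
- **That the article already concludes EMDR is safe.** It says the results will contribute to knowledge on whether it is.
- **That events after the last session are certainly not asked about.** Multimedia Appendix 2, on adverse events and dropouts, is not shown. A TAU or post-treatment query there cannot be excluded, although Clinical Safety Procedures ties that appendix to EMDR recording.
- **That two-arm collection would settle the controversy.** The power figures above say otherwise.

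None of this gives the adverse-event outcome a comparator. The scales measure average severity in the past one or two weeks and do not count discrete harms over four months.

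**Conclusion.** The point holds in limited form. Adverse events are a secondary outcome meant to inform safety, yet every description of their collection or reporting is restricted to EMDR: 12 scheduled queries in one arm and none described in the other. EMDR events therefore cannot be separated from the background rate. Suicidal-behaviour data after baseline in both arms amount to CSSRS windows covering 11.5% to 12.5% of follow-up, plus one undated attempt item.

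The primary outcome, the randomisation and the primary analysis are unaffected. The conclusion assumes that the unshown appendix does not contain a TAU query. The capture probabilities also assume independent events spread evenly over time, and the power figures use illustrative rates that the document does not give.

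**What to change.** 1. At 2 and 4 months, send both arms the same adverse-event and suicidal-behaviour items through REDCap, with recall running from the previous assessment. The items in Multimedia Appendix 2 may serve if they suit both arms.
2. Report the EMDR versus TAU risk difference with an exact 95% CI, labelled descriptive because power is low at 32 to 40 per arm.
3. Keep the EMDR session records in a separate table and do not pool them with the questionnaire data.
4. If TAU collection is not added, state that the adverse-event findings are an uncontrolled description of the EMDR arm, and limit the safety conclusion accordingly.

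The cost is a few minutes of extra questionnaire time at two existing assessments and a minor ethics amendment. Recruitment began in May 2021, so the items can be added only to assessments still to come; the report should say how many participants in each arm answered them. The change concerns measurement only and alters no clinical procedure.

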### Study Procedure

This study is being conducted in partnership with the outpatient mental health clinics of the Alberta Health Services Addiction and Mental Health, Edmonton Zone. Figure 1 shows the anticipated flow of subject enrollment and assessments.

Community clinicians will make a referral through email, fax, or phone to the RA. The research ethics board at the University of Alberta approved a waiver of consent to allow the RA to receive and screen referrals and contact the potential participants to set up a Zoom meeting to explain the study and obtain informed consent. If necessary, the RA can aid the potential participant in setting up Zoom and instructing the person on its use. During this initial Zoom meeting, the RA will obtain informed consent for participation in the study, which will be collected and managed using REDCap (Research Electronic Data Capture) tools hosted by the Women & Children's Health Research Institute at the University of Alberta, using a 2-factor authorization process [52]. Participants will be informed that they may withdraw their consent and opt out of the study at any time during the 4-month study period, whereas participant data may be withdrawn at any point before treatment begins.After obtaining consent, the RA will send a link from REDCap to the participant to complete the DES-II electronically. A DES-II score ≥34 will exclude a person from the study. If enrollment screening criteria are met, the participants will receive a psychiatric assessment by the study psychiatrist. The purpose of the psychiatrist assessment is to complete an in-depth assessment to rule out contraindications to web-based EMDR and to ensure eligibility criteria are met, including ruling out severe dissociation not apparent on the DES-II screening questionnaire. The psychiatrist will also perform a baseline diagnostic assessment according to *Diagnostic and Statistical Manual of Mental Disorders - 5* criteria to evaluate the baseline diagnoses. If the person appears suitable for the study, baseline self-report measures will be completed electronically (Table 1). Once the baseline measures are complete, REDCap will randomly assign the person to either the EMDR group or the TAU group using random computerized allocation.All patients will complete baseline and follow-up measures electronically through REDCap, as shown in Table 1.Patients in the EMDR treatment group will receive live, twice weekly EMDR through Zoom videoconferencing. The study therapist will take a relevant history, provide limited psychoeducation, and explain EMDR to the patient. After developing a safety plan with the participant, up to 5 standard preparation exercises will be completed before therapy (container, safe state, internal meeting place, safe place for parts, and updating the emotional circuits [53]). Patients will then receive EMDR, targeting the experiences or core beliefs associated with the SI. The standard EMDR protocol will generally be used, with the modification that the *future template* will be a *flashforward* of the *worst-case scenario future when suicide would again seem like an option*. Although the standard *future template* involves running a mental movie about the future, a *flashforward* targets the person’s mental representation of future events in a similar fashion as past events are targeted (see the paper by Logie and De Jongh [54] for details about this strategy).

**Table 1 table1:** Timing and content of study measures.

Measure	Content of measure	Timing of measures		
		Baseline	2 months after enrollment	4 months after enrollment
Demographic questionnaire	Demographics	✓^a^		
ACES^b^	Adverse childhood experiences	✓		
DES-II^c^	Dissociative symptoms	✓		✓
BSS^d^	Suicidal ideation	✓	✓	✓
CSSRS^e^—clinician rated	Suicidal ideation	✓		
CSSRS—past week (self-rated)	Suicidal ideation	✓	✓	✓
BDI-II^f^	Depressive symptoms	✓	✓	✓
PHQ-9^g^	Depressive symptoms	✓	✓	✓
GAD-7^h^	Anxiety	✓	✓	✓
IES-R^i^	PTSD symptoms	✓	✓	✓
DERS^j^	Emotional dysregulation	✓		✓

^a^Indicates the timing of the respective measures.

^b^ACES: Adverse Childhood Experiences Scale.

^c^DES-II: Dissociative Experiences Scale.

^d^BSS: Beck Scale for Suicide Ideation.

^e^CSSRS: Columbia Suicide Severity Rating Scale.

^f^BDI-II: Beck Depression Inventory-II.

^g^PHQ-9: Patient Health Questionnaire-9.

^h^GAD-7: Generalized Anxiety Disorder-7.

^i^IES-R: Impact of Events Scale Revised.

^j^DERS: Difficulties in Emotional Regulation Scale.

Some other modifications to the standard protocol are allowed. Specifically, intrusive or distressing memories may be targeted initially, if needed, instead of the first, worst, current, and future order of the standard protocol. If there is apprehension about doing EMDR, a flashforward of the worst thing that could happen may be used to address this resistance before targeting memories. This was reported as a successful strategy in an intensive treatment program [49]. In addition, therapists can use the EMDR early trauma protocol if there are significant attachment problems, add additional dual attention tasks to load working memory, or use shorter sets of bilateral stimulation if the standard protocol is not tolerated [55,56]. Strategies in the Jim Knipe EMDR Toolbox can also be used as needed [57]. Modifications to the standard protocol will be recorded in REDCap and reported on.

EMDR will specifically target the traumatic memories or core beliefs associated with the SI. These targets may be easily identified by the patient in some cases. Alternatively, the standard floatback method may be used to identify memory targets, or therapists may target the somatic urge or state associated with suicidal thoughts. This strategy of targeting states or urges has been utilized in EMDR protocols such as the *DeprEnd protocol* for depression and the *DeTUR protocol* for urges associated with substance use disorders [58,59]. Other possible targets for EMDR include memory of the circumstances surrounding the first occurrence of SI, memories at the origin of the negative beliefs associated with SI, or memories related to hopelessness and despair [21,58,60]. If escape fantasies, including the fantasy of escaping through suicide, emerge during memory processing, the participant may be encouraged to notice the fantasy rather than avoid or suppress it. In addition, if nightmares arise during the course of treatment, they can also be targeted directly using EMDR if clearly related to SI or the experiences being reviewed in therapy sessions.

Participants will be seen twice weekly until the therapy is completed (12 desensitization sessions in total). Symptoms and any adverse reactions will be recorded at the beginning of each session using a standard EMDR session progress note form.

